**Sample size/power calculation**

The main analysis is on opiate substation treatment (OST) in primary care and risk of death and in particular the comparison of methadone and buprenorphine*.

There will be at least 20,000 OST patients (extracted from CPRD GOLD patients) from 1998 to 2014 linked to NHS central registry and ONS mortality data, that will generate 67,000 person years (pys) follow-up (~32,000 on treatment and ~35,000 off) if censored 12 months after last OST. There will be over 700 deaths of which ~500 will be due to overdose. This will be the largest study in the UK with precise data on OST treatment exposure (including ~ 12000 pys on buprenorphine and 30,000pys on methadone). In addition, there will be approximately 10,000 and 12,000 person years in treatments lasting less than 1 month or greater than 12 months, and 3000 and 1200 person years follow-up in the first 4 weeks treatment on or immediately after methadone or buprenorphine treatment respectively.

Thus, there is sufficient power (> 90%) to determine whether:-

1. there is at least a halving of the risk of death during treatment on burpenorphine compared to methadone (i.e. 0.35% vs. 0.69% respectively) – which requires a sample of at least 922 in each group compared to 12,000 and 20,000 on buprenorophine and methadone
2. and sufficient power (80%) to test if the risk of death is at least a 1/3 lower on buprenorphine at (0.006%) compared to methadone (0.016%) in the first 4 weeks of treatment (1200 and 3000 person years respectively) – as indicated by unpublished analyses by Degenhardt on Australian mortality cohort(9).

In addition, there is sufficient power to corroborate that the risk of fatal overdose out of treatment at 0.8% is twice as high as the risk during treatment – which will require sample of at least 788 in and out of treatment compared to our sample of over 30,000 person years in each group; and that the risk of death in the 4 weeks after treatment at about 4.6% is 1/3 lower (3.0%) for people treated for short duration of treatment (< 1 month) compared to those treated for 12 months or longer – which will require sample of at least 3123 in each group compared to over 3500 and 3850 person years among those exposed to short or prolonged treatment respectively;

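### The required sample sizes of 922 and 788 per group are about ten times too small for the printed death risks; the claim of more than 90% power survives, but with a far thinner margin than the protocol implies

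*Protocol*

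**What the plan says.** All of this is in the Protocol, Sample size/power calculation. Under the lead-in "Thus, there is sufficient power (> 90%) to determine whether", the first item is that "there is at least a halving of the risk of death during treatment on burpenorphine compared to methadone (i.e. 0.35% vs. 0.69% respectively"), and its requirement is given as "which requires a sample of at least 922 in each group compared to 12,000 and 20,000 on buprenorophine and methadone".

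A later sentence says there is enough power to confirm that "the risk of fatal overdose out of treatment at 0.8% is twice as high as the risk during treatment". The size needed for this second comparison, with the data set against it, is put as follows: "which will require sample of at least 788 in and out of treatment compared to our sample of over 30,000 person years in each group". A third comparison in the same sentence, 4.6% vs 3.0% in the four weeks after treatment, is given a requirement of 3123 per group.

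Alpha, sidedness and formula are not stated. The section describes the follow-up as "32,000 on treatment and ~35,000 off" person-years, and elsewhere as "including ~ 12000 pys on buprenorphine and 30,000pys on methadone". The Limitations section names the buprenorphine–methadone mortality comparison as the key hypothesis.

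**The concern.** The figures look implausible before any formula is applied. With 922 per group, the expected deaths are 922 × 0.0035 = 3.2 and 922 × 0.0069 = 6.4. With 788 per group they are 788 × 0.004 = 3.2 and 788 × 0.008 = 6.3. Three deaths against six cannot give 90% power.

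The stake is how much data the key comparison can afford to lose. Setting 12,000 against 922 tells the reader that there is a 13-fold surplus on buprenorphine, so that losses hardly matter. The protocol itself contains several routes to loss:
- only a subset of patients is eligible for ONS linkage (Study population);
- the outcome section ends the risk period in 2011, while the power section counts patients to 2014;
- propensity-score matching is planned (Data/Statistical Analysis Plan).

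**Working it through.** **Inputs.** Risks 0.35% vs 0.69% and 0.4% vs 0.8% (0.4% being half of 0.8%), and the calibration case 3.0% vs 4.6%, all from the power section. Power is 90%, from the lead-in. Assumed, because not stated: two-sided 5% (z = 1.96 and 1.2816), equal groups, pooled-variance two-proportion formula with continuity correction.

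**Formula.** With d = |p1 − p2| and p̄ the mean risk:

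n = [1.96·√(2p̄(1−p̄)) + 1.2816·√(p1(1−p1) + p2(1−p2))]² / d²

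n′ = (n/4)·[1 + √(1 + 4/(n·d))]² (continuity-corrected)

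**Step 1: calibrate on the protocol's own 3123.** For 0.030 vs 0.046, p̄ = 0.038 and d = 0.016. n = (0.5300 + 0.3462)²/0.000256 ≈ 2,998.8 and n′ = 3,122.5, which rounds up to 3123. The assumed settings match a printed figure exactly.

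**Step 2: the same settings at the other printed risks.** For 0.0035 vs 0.0069, p̄ = 0.0052 and d = 0.0034. n = (0.1994 + 0.1303)²/0.00001156 ≈ 9,402 and n′ ≈ 9,982.

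| Risks | Uncorrected n | Corrected n | Printed | Corrected ÷ printed |
|---|---|---|---|---|
| 0.35% vs 0.69% | 9,402 | 9,982 | 922 | 10.8 |
| 0.345% vs 0.69% (exact halving) | 9,088 | 9,659 | 922 | 10.5 |
| 0.4% vs 0.8% | 7,832 | 8,324 | 788 | 10.6 |

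Other usual settings do not rescue the figures. With alpha 5%, one- or two-sided, power 80–90%, corrected or not, the first comparison needs 5,348 to 9,982 per group and the second 4,609 to 8,324. A Poisson rate formula, which suits person-years better, gives 9,137 to 9,453 for the first comparison at 90% power.

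**Step 3: what does give 922 and 788.** Under the Step 1 settings, 3.45% vs 6.9% gives 921.4, rounding up to 922, and 4% vs 8% gives 787.9, rounding up to 788. The rounded pair 3.5% vs 6.9% gives 952, so the match needs the exact half of 6.9%.

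**Step 4: power.** At 922 per group and the printed risks, power is 17–18%; at 788 per group it is 18%. At the planned 12,000 vs 20,000, power for 0.35% vs 0.69% is 98.4% (pooled, uncorrected) or 97.1% (log rate ratio). At 30,000 per group, power for 0.4% vs 0.8% exceeds 99.9%.

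**Step 5: margin for the key test (0.35% vs 0.69%).**
- Apparent: 12,000/922 = 13.0.
- Against equal groups: 12,000/9,982 = 1.20 (12,000/9,659 = 1.24 for an exact halving).
- At the planned 12:20 split, 90% power needs the following:

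| Method | Buprenorphine | Methadone | Surplus | Tolerated loss |
|---|---|---|---|---|
| Uncorrected | 7,640 | 12,730 | 1.57 | 36% |
| Continuity-corrected | 8,102 | 13,503 | 1.48 | 32% |
| Log rate ratio | 8,500 | 14,170 | 1.41 | 29% |

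The log-rate row comes from ((1.96 + 1.2816)/ln(0.0069/0.0035))² × (1/(12,000 × 0.0035) + 1/(20,000 × 0.0069)) = 0.708 of the planned person-years. On the uncorrected basis, power is 95% after a 20% loss, 88% with 60% of the person-years left and 81% with half left.

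**Step 6: person-years.** 12,000 + 20,000 = 32,000, which agrees with the on-treatment total. 12,000 + 30,000 = 42,000, which does not.

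**The case against.** The strongest reply is that the plan's conclusion is true. It claims more than 90% power at 12,000 vs 20,000, and the correct value is 97–98%; the in-versus-out comparison is safer still. This is an observational study that takes every eligible patient in the database, so nobody recruits to 922 or 788 and no analysis uses them. All of that stands, and it limits the point to a wrong requirement and a wrong margin.

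A fair reader would add that the 1.2-fold figure assumes equal groups although the planned split is 12:20. That is right, which is why 1.4- to 1.6-fold is given beside it. The person-years set against 922 are also internally consistent: only the separate 30,000 for methadone conflicts, and the power statement does not use it. It may include time off treatment, but the text does not say so.

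Three stronger readings are tempting and not supported. A reader might infer that the key test is underpowered as planned, or that any loss of data would make it so; Steps 4 and 5 show neither is the case. A reader might also link the slip to the December 2015 amendment, which reports underpowered analyses. That amendment attributes the problem to fewer deaths than expected, with only 30% of them overdose or drug related, and not to the sample-size formula. It discloses reduced power but does not correct 922 or 788.

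**Conclusion.** The point holds as an arithmetic error with a limited consequence. At the printed risks the requirements are understated by a factor of about 10.5 (10.8 if 0.35% is taken literally). The exact replacements rest on an assumed two-sided 5% test with 90% power and continuity correction. The order of the error does not: every usual setting tried gives several thousand per group.

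That the risks were entered ten times too large is an inference. Three exact matches under one set of settings make it likely, but the authors' inputs are not shown.

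The conclusion of more than 90% power survives on the planned person-years. The impression of a 13-fold reserve for the key hypothesis does not, since about 30–36% of the person-years is all that can be lost before power drops below 90%.

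**What to change.** In the Sample size/power calculation section:

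1. Replace 922 with about 9,980 (or 9,660 if an exact halving, 0.345% vs 0.69%, is meant) and 788 with about 8,320. If no continuity correction is wanted, use about 9,400 (9,090) and 7,830, and recompute 3123 on the same basis (2,999). Use one set of inputs and one method throughout.
2. State alpha, sidedness, power and formula.
3. Report power at the person-years actually available after linkage, end date and matching, and the minimum that keeps 90% at the planned split: about 7,640 and 12,730 uncorrected, 8,100 and 13,500 continuity-corrected, or 8,500 and 14,170 on the log-rate scale.
4. Reconcile the 30,000 methadone person-years with the 20,000 in the power statement and the on-treatment total of about 32,000, or say what the 30,000 includes.

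The cost is a rewrite of one section. No new data or change of design is needed; the stated margin simply becomes less favourable.

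### The 80% power claimed for mortality at least one third lower on buprenorphine in the first 4 weeks belongs to a 62.5% reduction; for one third it is about 24%

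*Protocol*

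**What the plan says.** The Protocol, Sample size/power calculation, names the comparison of methadone and buprenorphine as the main interest and makes two power claims for it. The second concerns treatment onset: "sufficient power (80%) to test if the risk of death is at least a 1/3 lower on buprenorphine at (0.006%) compared to methadone (0.016"%). The follow-up is stated as "in the first 4 weeks of treatment (1200 and 3000 person years respectively"), buprenorphine first. No alpha, sidedness, test or formula is given, and the rates are attributed to unpublished analyses of an Australian cohort.

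Two other statements in the same section matter. The paragraph before the list introduces these person-years as "3000 and 1200 person years follow-up in the first 4 weeks treatment on or immediately after methadone or buprenorphine treatment respectively". The paragraph after the list uses the same fraction for a different contrast: "the risk of death in the 4 weeks after treatment at about 4.6% is 1/3 lower (3.0"%).

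**The concern.** The words and the figures of item 2 describe different effects. One third lower than 0.016 is about 0.0107, but the figure used is 0.006. Because the claim is worded as at least one third, a reader will take one third as the smallest difference the study can reliably detect. Loose phrasing does not explain it away: 3.0% against 4.6% in the same section is 1 − 3.0/4.6 = 34.8% lower, so there the expression carries its ordinary meaning.

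The percent signs are a second difficulty, since risks that small would produce almost no deaths in the stated follow-up.

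The Protocol's statistical plan makes the comparison by modality at different periods on and off treatment its main analysis. Item 2 is the only power statement for the onset period. If it is believed, an onset result without a clear difference could be taken as evidence against a one-third difference that the study would in fact miss about three times in four.

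**Working it through.** **Inputs from the Protocol, Sample size/power calculation.** Buprenorphine: figure 0.006, 1,200 person-years. Methadone: figure 0.016, 3,000 person-years. Claimed power: 80%.

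**Assumption.** Two-sided alpha of 0.05 (z = 1.96), because none is stated.

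**Step 1: the effect in the figures.** 0.006/0.016 = 0.375, so the reduction is 1 − 0.375 = 62.5%. This holds whatever the unit.

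**Step 2: the figures as printed, in percent.** Expected deaths are 1,200 × 0.00006 = 0.07 and 3,000 × 0.00016 = 0.48. Power is 0.0% (exact conditional), 1.9% (pooled two-proportion) and 4.3% (log-rate Wald). The claimed 80% cannot come from this reading.

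**Step 3: reproducing the 80%.** Read the figures as 0.006 and 0.016 per person-year. Expected deaths are 1,200 × 0.006 = 7.2 and 3,000 × 0.016 = 48.

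- Pooled two-proportion test: power = Φ[(|p1 − p2| − 1.96 × SE0)/SE1].
  - Pooled rate = (7.2 + 48)/4,200 = 0.01314.
  - SE0 = √[0.01314 × 0.98686 × (1/1,200 + 1/3,000)] = 0.00389.
  - SE1 = √[0.006 × 0.994/1,200 + 0.016 × 0.984/3,000] = 0.00320.
  - Power = Φ[(0.010 − 0.00762)/0.00320] = Φ(0.74) = 77.1%.
- Square-root Poisson test: power = Φ[2(√0.016 − √0.006)/√(1/1,200 + 1/3,000) − 1.96] = Φ(0.0981/0.0342 − 1.96) = 81.9%.
- Log-rate Wald test: power = Φ[|ln 0.375|/√(1/7.2 + 1/48) − 1.96] = Φ(0.981/0.400 − 1.96) = 68.9%.
- Other tests: Poisson likelihood ratio 81.9%, arcsine 82.3%, exact conditional 75.4%, continuity-corrected 71.3%.

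The common tests therefore give about 69% to 82%. Two approximations run higher: unpooled variance 87.9% and Schoenfeld 90.9%. The stated 80% is reproduced, but for a 62.5% reduction.

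**Step 4: a true one-third reduction.** The buprenorphine rate is 0.016 × 2/3 = 0.01067, giving 12.8 expected deaths against 48.

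- Pooled: pooled rate = 60.8/4,200 = 0.01448, SE0 = 0.00408, SE1 = 0.00375. Power = Φ[(0.00533 − 0.00800)/0.00375] = Φ(−0.71) = 23.9%.
- Log-rate Wald: Φ[0.405/√(1/12.8 + 1/48) − 1.96] = Φ(−0.67) = 25.1%.
- Other two-sided tests: continuity-corrected 19.3%, exact conditional 21.2%, likelihood ratio 27.1%, square-root 27.4%, arcsine 27.7%, unpooled 29.6%, Schoenfeld 29.7%.
- One-sided 5%, pooled: 35.7%.

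No variant comes near 80%. At the cohort's own 1,200:3,000 ratio, 80% power (pooled) would need about 5,245 and 13,113 person-years.

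**Step 5: could the figures be 4-week risks?** Treating each 4-week window as a unit gives 1,200 × 13 = 15,600 and 3,000 × 13 = 39,000 windows. At 0.6% and 1.6% per window that is 93.6 + 624 = about 718 deaths in these windows alone. The same section expects just over 700 deaths in the whole study, so this reading is not tenable. At the printed percentages per window, expected deaths are 0.94 and 6.24 and pooled power is 10%.

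**The case against.** The strongest reply is that the calculation itself is sound. Read as rates per person-year, the figures give 82% by a Poisson likelihood-ratio test, and a rate ratio of 0.375 is close to a third of the methadone rate, so item 2 may be a slip of wording. Much of this stands. A reader might infer that the 80% is a computational failure and should be replaced by the pooled 77%. The Protocol does not support that, because it names no test and several ordinary tests give about 80%. What fails is the link between the 80% and the effect named in words.

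A reader might also infer that the person-years are wrong because they mix onset with post-treatment time. The wording that introduces them is ambiguous: each window may contribute these amounts, or the two may be pooled. Item 2 itself assigns them to the first 4 weeks of treatment, which favours the first reading. That needs about 4,200 × 13/20,000 = 2.7 episodes per patient, which is not implausible when episode number is a planned covariate. It is therefore a point to confirm. The Protocol gives no split from which a lower power could be derived.

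It can also be said that the cohort is an existing database, so no recruitment target depends on item 2. The Limitations section cautions against over-interpreting single tests, and the December 2015 amendment concedes that analyses were underpowered. The first point limits the consequence to interpretation. The caution concerns multiplicity, and the amendment concerns too few deaths and the low share that were overdose or drug related. Neither corrects item 2.

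**Conclusion.** The concern holds. Item 2 attaches 80% power to a one-third reduction, but its figures are a 62.5% reduction, and the 80% is roughly right only for that effect. For one third, power is about 24%, within roughly 19% to 30% across two-sided methods.

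This rests on three assumptions: two-sided 5% testing; the figures being 0.6 and 1.6 per 100 person-years, the only reading tried that both approaches 80% and fits the expected total of deaths; and all 1,200 and 3,000 person-years being onset time. The mismatch between one third and 62.5% depends on none of them. If the printed percentages were literal, power would be about 0% to 4% for the 62.5% reduction and no better for one third.

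**What to change.** In item 2 of the sample size section:

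- Check the two figures against their source and print them with the right unit. If they are rates of 0.6 and 1.6 per 100 person-years, say so and remove the misplaced percent signs.
- Describe the contrast as a 62.5% reduction (rate ratio 0.375) with roughly 80% power, naming the test, alpha and sidedness behind the number.
- Add that power for a one-third reduction is only about 24%, and that an onset result without a clear difference will not be read as excluding a one-third difference.
- State whether the 1,200 and 3,000 person-years are onset time only. If they include time after treatment ends, give the onset share and lower the stated power for both effects.

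The cost is wording and a short recalculation. Data extraction and planned analyses do not change, but the power reported for the onset comparison becomes less favourable.

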**Background**

Opiate substitution treatment (OST) is the key treatment for heroin dependence and has been shown to have multiple benefits, including reductions in drug related crime, blood borne virus transmission, and improvements in social functioning(1-5). Prescribed OST in the community includes methadone, buprenorphine, and dihydrocodeine(1, 6). There are approximately 200,000 people who inject drugs (PWID), half exposed to drug treatment annually, mainly OST (75%) but also non-pharmacological treatments delivered in specialist drug agencies and residential units. OST is effective because it reduces heroin injection and is cost effective because of reductions in drug related crime and health harms(7). Observational studies have shown that the risk of mortality is reduced during opiate substitute treatment(8-12). Buprenorphine has been shown to be as good as methadone at treatment retention(13), and hypothetically is less likely to cause fatal overdose than methadone(14). In France, ecological analyses suggest that trends in overdose deaths are negatively associated with increases in buprenorphine prescription(15). However, direct comparative evidence on the risk of death during buprenorphine vs. methadone is yet to emerge.

Several recent studies also have highlighted that there is a period of very high mortality risk (>8 times higher than mortality risk during treatment) in the first few months immediately after treatment cessation (9-11, 16). In the UK analyses of primary care information have suggested that the risk of death in those who receive OST is twice as high among men compared to women, and is raised at the beginning and end of treatment, and maybe higher in those co-prescribed benzodiazepines(11, 17). In Australia the risk of death at treatment onset was greater than in the UK, with some evidence to suggest that the mortality risk at treatment onset was lower among those initiated onto buprenorphine compared to methadone, but these benefits may be offset by a shorter duration of treatment for those on buprenorphine compared to methadone(9). The evidence base on other drug treatments (residential rehabilitation, detoxification, and psychological treatments) is more limited; but studies also suggest that the risk of mortality is reduced during treatment and elevated after treatment (10, 18).

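### The 80% power stated for the first-4-weeks buprenorphine versus methadone comparison does not follow from the printed rates, and on the one workable reading it probably rests on rates too high for the UK

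*Protocol*

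**What the plan says.** The power claim is item 2 of the protocol's Sample size/power calculation section. It asserts "sufficient power (80%) to test if the risk of death is at least a 1/3 lower on buprenorphine at (0.006", where the last figure is printed as a percentage. The comparator risk and the follow-up time come next: "compared to methadone (0.016%) in the first 4 weeks of treatment (1200 and 3000 person years respectively". The source named for this is unpublished work "on Australian mortality cohort(9".

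Four other statements bear on it:

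- The same section describes the person-years as "3000 and 1200 person years follow-up in the first 4 weeks treatment on or immediately after methadone or buprenorphine treatment respectively".
- Item 1 of that section gives the death risk during treatment on buprenorphine and methadone as "i.e. 0.35% vs. 0.69% respectively".
- The Background, citing the same Australian cohort, says "In Australia the risk of death at treatment onset was greater than in the UK".
- The Background also says of UK patients that the risk of death "is raised at the beginning and end of treatment".

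Item 2 gives no UK onset rate, no adjustment from Australia to the UK and no sensitivity range.

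**The concern.** When death rates are compared, power depends on the number of deaths, so the baseline rate and its unit decide the answer. Two things are doubtful here.

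1. **Unit.** The printed methadone onset risk, 0.016%, is far below the 0.69% given in item 1 for methadone treatment as a whole, although the Background says UK risk is raised at onset. A percent sign on a figure that was already a proportion would explain this, but the text does not say so.
2. **Source population.** Once the figures are rescaled to a plausible level, the only source named for them is a cohort whose onset mortality the protocol itself describes as higher than in the UK. The patients to be analysed are from UK general practice.

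The Limitations section names methadone versus buprenorphine as the key hypothesis, and item 2 is one of its two power claims. If onset power is overstated, a null result in the first four weeks could be read as no difference when there were too few deaths to show one.

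**Working it through.** **Inputs.** Person-years: 3,000 methadone, 1,200 buprenorphine (item 2). Rates: 0.016 and 0.006, printed with percent signs (item 2). Rate ratio: 0.006/0.016 = 0.375, a 62.5% reduction. Significance level: not stated; two-sided 5% assumed.

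**Formulas.** Expected deaths = rate × person-years. With d the rate difference, SE0 the pooled (null) standard error and SE1 the unpooled one:

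- Pooled: power = Φ((d − 1.96·SE0)/SE1)
- Unpooled: power = Φ(d/SE1 − 1.96)
- Wald on the log rate ratio: power = Φ(|ln RR|/√(1/D1 + 1/D2) − 1.96), where D1 and D2 are the expected deaths
- Likelihood-ratio test: enumerated over two independent Poisson counts; actual size about 5.2%
- Exact conditional Poisson test

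**Step 1: rates as printed, per person-year.** Deaths: 3,000 × 0.00016 = 0.48 and 1,200 × 0.00006 = 0.07, about 0.5 in all. Pooled: d = 0.0001, SE0 = 0.000392, SE1 = 0.000321, so Φ(−2.08) = 1.9%. Likelihood-ratio 0.15%; exact under 0.01%. The Wald and unpooled approximations, unreliable with so few deaths, give 4% and 5%. The 80% is not reproduced.

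**Step 2: rates as printed, as 4-week risks.** There are 13 four-week periods in a year, so 0.016% is about 0.21% a year. Deaths: 3,000 × 13 × 0.00016 = 6.2 and 1,200 × 13 × 0.00006 = 0.9. Pooled power is about 10%. Not reproduced.

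**Step 3: rates read as 1.6 and 0.6 per 100 person-years.** Deaths: 3,000 × 0.016 = 48 and 1,200 × 0.006 = 7.2.

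- Pooled: mean rate 55.2/4,200 = 0.01314, SE0 = 0.00389, SE1 = 0.00320, so Φ((0.010 − 0.00762)/0.00320) = Φ(0.74) = 77%
- Wald: 0.981/√(1/48 + 1/7.2) = 0.981/0.400 = 2.45, so Φ(0.49) = 69%
- Exact 75%; likelihood-ratio 82%; unpooled Φ(3.13 − 1.96) = 88%

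This is the only reading that comes near 80%, and the result depends on the test.

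**Step 4: a lower UK baseline.** The documents give no UK onset rate, so the methadone rate is varied with the rate ratio held at 0.375. The lowest value, 0.69, is item 1's risk for methadone treatment overall, taken per 100 person-years. It is a rough floor, because UK risk is said to be raised at onset.

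| Methadone rate per 100 person-years | Deaths, methadone / buprenorphine | Likelihood-ratio | Pooled | Wald | Unpooled |
|---|---|---|---|---|---|
| 1.6 | 48 / 7.2 | 82% | 77% | 69% | 88% |
| 1.4 | 42 / 6.3 | 77% | 70% | 63% | 83% |
| 1.2 | 36 / 5.4 | 70% | 63% | 57% | 77% |
| 1.0 | 30 / 4.5 | 62% | 53% | 49% | 69% |
| 0.69 | 20.7 / 3.1 | 47% | 37% | 36% | 54% |

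At 1.2 or below, every method falls short of 80%.

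**Two related checks at 1.6 per 100 person-years.** A reduction of exactly one third would have 24% power (pooled). If only half of the stated person-years were onset time, since the section describes them as on or just after treatment, pooled power at 1.6 versus 0.6 would be 43%.

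**The case against.** The strongest reply is that the source-population argument works only after the printed figures are multiplied by 100. Taken literally, 0.016% is too low for UK patients, not too high. That is correct, and it is why the unit must be settled first.

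A reader might infer that the 80% is sound at the Australian rates and that the UK study will certainly have fewer onset deaths and less power. The documents do not support that. Even at 1.6 versus 0.6, only some tests reach 80%. The sentence citing the Australian analyses could refer to the relative effect and not to the absolute rates. That it covers the rates is the natural reading, because they directly precede it and no other source is named, but it remains an inference. The Background gives no size for the Australia–UK gap. A small gap would cost little: at 1.4, likelihood-ratio power is still about 77%.

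It can also be said that the consequences are limited. This is a database extract, so power does not set recruitment. The Limitations section undertakes not to over-interpret single tests. The December 2015 amendment admits fewer deaths than expected and underpowered analyses. All of this tempers the concern, but the amendment does not revisit the first-4-weeks comparison, and item 2 still states 80% without qualification.

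**Conclusion.** The point holds in this form: the unqualified 80% in item 2 is not supported by its own inputs. As printed, power is about 2% or less by the pooled, likelihood-ratio and exact methods. Rescaled to 0.6 and 1.6 per 100 person-years, it is 69% to 82% by four two-sided methods and 88% with an unpooled variance.

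On the rescaled reading, the Background gives reason to expect a lower baseline, and so lower power, in UK patients. The size of that loss is not known. Over methadone rates from 1.6 down to 0.69, power falls from 82% to 47% (likelihood-ratio) or from 77% to 37% (pooled).

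This rests on four assumptions: a two-sided 5% test, a rate ratio fixed at 0.375, all of the stated person-years being onset time, and absolute rates taken from the Australian cohort. The last affects only the expected further fall, not the failure of the printed figures to give 80%.

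**What to change.** In item 2 of the Sample size/power calculation:

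1. Correct the two rates and state their unit (per person-year or per 4-week period), their source, and the test and significance level used.
2. Say whether the Australian analyses supplied the absolute rates, the rate ratio or both. Take only the rate ratio from them, and use a UK onset rate as the baseline. The team's earlier UK primary care cohort (reference 11) is the obvious place to look, but the protocol does not show that it reports a methadone-specific first-4-weeks rate.
3. If no such rate is available, print the power, or the smallest rate ratio detectable with 80% power, across about 0.7 to 1.6 per 100 person-years.
4. Confirm how many of the 3,000 and 1,200 person-years are onset time, and make the described reduction match the rates.
5. Replace the flat 80% statement with the result.

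The cost is one recalculation and a few changed sentences. No further data or patients are needed. The downside is a less favourable stated power for the onset comparison.

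### The power claim for death in the 4 weeks after short versus long treatment rests on 7,350 person-years in total, but the same section gives 4,200 for four-week windows at all durations

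*Protocol*

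**What the plan says.** All the figures stand in the Protocol, Sample size/power calculation.

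- The contrast, from a base of about 4.6% (annualised) after stopping: the rate "is 1/3 lower (3.0%) for people treated for short duration of treatment (< 1 month) compared to those treated for 12 months or longer".
- The requirement and what is set against it: "which will require sample of at least 3123 in each group compared to over 3500 and 3850 person years among those exposed", the first figure for short and the second for long treatment.
- Four-week time by drug, all durations: "3000 and 1200 person years follow-up in the first 4 weeks treatment on or immediately after methadone or buprenorphine treatment respectively".
- The same pair is used again in numbered item 2, for the start of treatment alone: "in the first 4 weeks of treatment (1200 and 3000 person years respectively").
- Time by treatment length: "10,000 and 12,000 person years in treatments lasting less than 1 month or greater than 12 months".

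The section also expects at least 20,000 patients, about 32,000 person-years on treatment and 35,000 off, and over 700 deaths. It states no alpha. For this contrast it says only that power is sufficient; the figure above 90% introduces the numbered list that precedes it. The section Exposures, outcomes and covariates defines four duration classes, so short and long treatment are two of four.

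**The concern.** The outcome is death in the 4 weeks after stopping, so the relevant exposure is person-time inside that window. Two of four duration classes are given 1.75 times (7,350 / 4,200) the four-week time that the section gives for methadone and buprenorphine at all durations. If the time at risk is not there, the stated power is not there either.

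The contrast is secondary, but it has consequences. Treatment duration is among the modifiable factors in the over-arching hypothesis (Objective, specific aims and rationale). Short versus long treatment is a planned propensity-score comparison, and changing duration is one of the model scenarios (Data/Statistical Analysis Plan). A reader told that power was sufficient could take a null result as evidence that treatment length makes no difference to risk after stopping.

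**Working it through.** **Inputs from the Protocol:** rates 0.046 and 0.030; 3,123 per group; 3,500 and 3,850 person-years; 3,000 and 1,200 four-week person-years; 12,000 person-years in treatments over 12 months; 32,000 on treatment; over 700 deaths. **Assumed:** two-sided alpha of 0.05, since none is stated.

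**1. Reproduce the 3,123.** With d = 0.016 and mean proportion p = 0.038:

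n = [1.960·√(2·p·(1−p)) + 1.282·√(0.046·0.954 + 0.030·0.970)]² / d² = (0.5300 + 0.3462)² / 0.000256 = 2,999.

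With continuity correction, (n/4)·[1 + √(1 + 4/(n·d))]² = 3,123. This is an exact match at 90% power. A Poisson rate-difference formula gives 3,120 person-years per group, so the requirement is sound.

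**2. Which unit?** A four-week window is 4/52 year, so 7,350 person-years is 7,350 × 13 = 95,550 windows. If 3.0% and 4.6% were risks per window, the deaths would be 45,500 × 0.030 + 50,050 × 0.046 ≈ 3,667, against just over 700 in the whole cohort. The percentages fit only as annual rates, so person-years are the right unit.

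**3. Compare required, claimed and available time.**

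| Quantity | Person-years |
|---|---|
| Required, 90% power: 2 × 3,123 | 6,246 |
| Required, 80% power, no continuity correction: 2 × 2,241 | 4,482 |
| Claimed for the two classes: 3,500 + 3,850 | 7,350 |
| Four-week time, both drugs, all durations: 3,000 + 1,200 | 4,200 |

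Even the 80% requirement exceeds 4,200.

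**4. A check on the long class that does not use the 4,200.** Each completed treatment adds at most 4/52 year after stopping. Therefore 3,850 person-years needs 3,850 × 13 = 50,050 treatments of at least 12 months, and so at least 50,050 person-years on treatment. The section gives about 32,000 on treatment in total. From the other direction, 12,000 person-years in treatments over 12 months is at most 12,000 such treatments, which yield at most 12,000 × 4/52 = 923 post-treatment person-years. Using all 32,000 would give at most 2,462, still below 3,123.

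**5. Power at the available time.** Power = Φ[(d − 1.960·s₀)/s₁], where s₀ is the pooled and s₁ the unpooled standard error of the difference.

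- 3,500 and 3,850: s₀ = 0.004487, s₁ = 0.004440, z = 1.623, power 94.8% (94.1% with continuity correction).
- 2,100 and 2,100: s₀ = 0.005900, s₁ = 0.005895, z = 0.752, power 77.4%. With continuity correction, which reduces d by 1/2,100, z = 0.672 and power is 74.9%. Poisson formulas give 75–76%.
- 1,909 and 2,291 (the 4,200 split 10:12): power 76.7%.
- 3,500 and 923 (long class capped as in step 4): power 65.5%.

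The equal split gives all 4,200 to the post-treatment window and nothing to treatments of 1 to 12 months. It is a favourable case, and step 4 suggests the long class could not reach 2,100.

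**The case against.** **The 3,500 and 3,850 may not be four-week windows.** The sentence speaks of person-years among those exposed to short or prolonged treatment and does not say which follow-up is counted. The figures are 10% and 11% of the roughly 35,000 off-treatment person-years, so they may be wider follow-up. This cannot be excluded, and on that reading the time could exist. It does not save the power claim, because time outside the window is the wrong denominator for a rate inside it.

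**The 4,200 is not every window.** It covers methadone and buprenorphine, while dihydrocodeine episodes are also included. They would have to supply at least 7,350 − 4,200 = 3,150 person-years of four-week time, which does not sit with a drug the Protocol describes as used occasionally.

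**Stronger readings that a reader might infer are not supported:**

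- Neither 3,500 nor 3,850 alone exceeds 4,200; only their sum does.
- Halving the 4,200 between start and post-treatment windows would give about 48% power (1,050 each), and spreading that half over four classes about 27% (525 each). The plan gives neither split, and numbered item 2 assigns the full 1,200 and 3,000 to the start window, which argues against halving.
- The 10,000 person-years in treatments under 1 month might look impossible, since it would take about 118,000 episodes if it is all on-treatment time. If it includes up to 12 months of follow-up, the difficulty goes away. The section does not say which is meant.

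**The plan partly guards against over-reading.** The Limitations section promises caution with single tests and names buprenorphine versus methadone as the key hypothesis. The December 2015 amendment reports that the 2014 linkage left analyses underpowered and seeks a larger one. Both points stand and limit the weight of this one. Neither corrects the person-years or withdraws the claim of sufficient power.

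**Conclusion.** The point holds. The requirement of 3,123 per group is right; the person-years set against it are not usable as stated. They either contradict the 4,200 in the same section or measure a different period from the outcome. The long-treatment figure also fails on its own: the plan's 12,000 person-years allow about 920 post-treatment four-week person-years, not 3,850.

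On the section's four-week total, power is at most about 77% (75% with continuity correction), against about 95% at 3,500 and 3,850. It falls further, by an amount the plan does not fix, once treatments of 1 to 12 months are counted or if the 4,200 also covers the start window. These figures assume a two-sided 5% test, annual rates of 3.0% and 4.6%, and no material dihydrocodeine time. The 90% target is inferred from the exact match, because the plan gives no number for this contrast. The point concerns a secondary contrast and leaves the methadone–buprenorphine comparison untouched.

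**What to change.** 1. Recount post-treatment four-week person-years from episode counts by duration class: 4/52 year per completed treatment, cut short at death, restart of treatment or other end of follow-up.
2. Reconcile 3,500 and 3,850 with the 4,200. State whether the 4,200 covers the start window, the post-treatment window or both, and whether the 10,000 and 12,000 are on-treatment time or include follow-up.
3. State that 3.0% and 4.6% are rates per 100 person-years, and give the alpha and power used.
4. Restate the power as the recount gives it or, until then, as at most about 77%.
5. Report the contrast as a rate ratio with a confidence interval and drop the claim of sufficient power. The Poisson models already planned produce incidence rate ratios.

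The cost is arithmetic, wording and a less favourable stated power. No data collection or model changes.
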